## Abstract

**Background:**

Adult participation in sport is associated with important positive psychosocial outcomes. Despite the multitude of benefits that have been linked to sport participation, adult participation rates in Canada remain low. Parents with young children represent a demographic that may benefit considerably from sport participation, given the prevalence of inactivity coupled with increased levels of psychosocial distress among this group. This study aims to evaluate the efficacy of two types of sport participation (individual sport and team sport) on key psychosocial outcomes compared with a “personal time” control condition among parents with young children.

**Methods/design:**

The three-arm, parallel design, single-blind, randomized controlled trial will compare a team sport condition, an individual sport condition, and a “personal time” control condition over 3 months. Parents are eligible if they have a child under 13 years of age, are not participating in a sport at baseline, and are not meeting Canadian Physical Activity Guidelines. Psychosocial variables (quality of life, relationship satisfaction, social functioning, parental stress, and enjoyment) will be assessed at baseline, 6 weeks, and 3 months. A total of 161 parents have been recruited thus far from the Greater Victoria region in British Columbia, Canada. The study is ongoing with a target goal of 240 participants and an anticipated completion date of December 2021.

**Discussion:**

This protocol describes the implementation of a randomized controlled trial that evaluates the effectiveness of sport participation for increasing positive psychosocial outcomes. This information could prove useful for future adult sport participation and potentially inform public health initiatives involving parents and families.

**Trial registration:**

ClinicalTrials.gov, NCT02898285. Registered 13 September 2016.

## Background

Recreational sport participation among adults is associated with a multitude of positive psychological and social health outcomes, including overall psychological well-being/life satisfaction, lower stress, higher social functioning, greater vitality, enjoyment, and a sense of community belonging when compared with adults who do not participate in sports [1]. This plethora of beneficial outcomes are well aligned with the key psychosocial health objectives of the Canadian Sport Policy [2]. Notably, team sport participation has been associated with even higher levels of these beneficial outcomes when compared with adults who participated in individual sports [3], an added benefit proposedly due to the social nature of team sports [1, 4]. Sport participation may also serve the dual aim of increasing physical activity (PA) to reap the well-established physical and psychological benefits associated with regular PA, such as reduced risk for chronic disease and premature mortality, reduced depression and anxiety, and improved overall quality of life [5].

Despite the array of positive psychosocial outcomes emerging from early-phase research on sport participation, few adults participate in sports. Indeed, participation rates among Canadians remain alarmingly low, with convincing evidence that sport participation declines steeply from late adolescence (54% participation) to adulthood (23% participation) [6]. To contextualize this finding, adult participation rates are much lower than in countries with similar climates, such as those in Scandinavia (42% participation) [7, 8], as well as countries in northern Europe (40%) [8], and compared with countries with similar population/economic distribution, such as Australia (56%) [9, 10]. Unsurprisingly, improving sport participation is a priority of the Canadian Sport Policy [2] and continues to be a critical issue in Canada [11].

When considering low participation rates among adults and potential psychosocial benefits, some groups may have a greater possibility to benefit. One such subset may be parents with young children. Given the demands of parenthood, parents of young children often report higher levels of psychosocial distress, such as increased depressive symptoms, lower vitality, and social isolation compared with age-matched adults without children [12–14]. Importantly, parents also report a significant decline in overall PA, inclusive of sport participation [15–17]. To this end, in a systematic review examining PA in studies with longitudinal designs, parenthood emerged as a significant predictor of PA decline [18]. This PA decline among parents is of particular concern because of the ensuing unlikelihood of meeting the public health guidelines recommended to optimize benefits [19]. Clearly, parents represent an important sport promotion demographic that may stand to gain considerable psychological, social, and health benefits.

To date, there has been no experimental investigation into the effects of sport participation on key psychosocial outcomes among parents. Furthermore, the effects of an individual sport versus a team sport have not been investigated empirically in the context of parents. This is a noteworthy limitation of prior research, given the promising effects of sport participation on psychological and social health [1]. Indeed, Eime and colleagues [1] recommended further investigation into the causal link between sport participation and psychosocial outcomes. To our knowledge, this study will be the first randomized controlled trial to examine this relationship. Therefore, the purpose of this paper is to describe the protocol of a study aiming to evaluate the efficacy of two types of sport participation (individual sport and team sport) regarding key psychosocial outcomes compared with a “personal time” control condition (a suitable comparator because it is time spent away from children that is not active in nature) among parents with young children.

## Methods/design

### Theoretical framework

Although the primary aim of the study is focused on sport participation outcomes, a secondary objective is to understand the mechanisms involved in sport participation behavior among parents. Theoretical frameworks act as useful guides for understanding behavior. Although many theories have been applied to understand sport participation, the Sport Commitment Model of Scanlan and colleagues [20] offers a suitable framework because it was specifically designed to examine reasons why individuals continue their participation in sport.

According to the model, commitment (i.e., desire and resolve to continue) is the primary mediator of sport participation. Because the model was built on hedonic theory [21] and intrinsic motivation [22], enjoyment (pleasure, fun, liking of sport) is thought to be the primary motive behind participation. There are four additional antecedents that are considered important to sport commitment: involvement alternatives (the attractiveness of the most preferred alternative), personal investment (personal resources put into the activity), social constraints (expectations or norms that create feelings of obligation), and involvement opportunities (valued opportunities present only through continued involvement).

The model has sound validation in various sport domains, including amateur youth sport, elite-level sport, health club fitness participation, and competitive sport among adolescents [20, 23–25]. Studies show that all five of the proposed antecedents of the model can predict commitment and that commitment reliably predicts sport participation. However, there is a paucity of research applying the model in a recreational sport setting among adults. To this end, only one study has applied the model to understand adult recreational sport [26]. This study sought to validate the sport commitment model in an adult recreational setting, namely tennis. Acceptable indices of fit indicated that the model has utility in understanding adult recreational sport participation. Furthermore, the model seems particularly applicable to parents because relevant antecedents of participatory behavior such as alternatives (child care and support, domestic activities), involvement opportunities (friendship and social interaction), and social expectations may play key roles in defining who continues to participate in sports. Finally, the model may assist in identifying potential mechanisms for the psychosocial outcomes. The present study aims to examine the conjecture that enjoyment and opportunities for social involvement act as key mediators for team sport participation over individual sport involvement [27, 28]. In sum, the present study seeks to fill a gap in the contemporary literature by examining the effects of both individual and team sport compared with a control condition, as well as the social and enjoyment mechanisms proposed as mediators of this relationship through application of the Sport Commitment Model [20].

### Pilot research

This research builds on both the extant literature and several pilot projects. First, a systematic review by Eime and colleagues [1] on sport participation and psychosocial outcomes provides valuable data from which the rationale for the experimental design was drawn. In addition, a community survey of 76 inactive parents residing in Greater Victoria, British Columbia, Canada, with children under the age of 13 years was conducted in order to explore the types of sports in which parents would have the greatest interest. Responses for the survey aligned with Canadian adult sport preferences [6]: The majority of parents chose soccer, basketball, ice hockey, dragon boating, and volleyball as preferred team sports, whereas the most preferred individual sport programs included running, swimming, and cycling. Finally, an environmental scan was conducted that investigated all of the adult recreational team sport and individual sport programs in Greater Victoria as well as adjacent licensed childcare opportunities. The scan established that all of the preferred sports from the survey had leagues/programs that run in every season. The well-matched and accessible sport and childcare opportunities indicated the plausibility of sport participation required for this study.

### Present research aims and hypotheses

The primary research question is whether a team sport condition increases positive psychosocial outcomes (quality of life, relationship satisfaction, social functioning, perceived parental stress, enjoyment) compared with an individual sport condition and a “personal time” control condition involving a choice-based pastime spent away from children. We hypothesize that the team sport condition will result in significantly greater changes in psychosocial outcomes than the other two conditions at the primary endpoint (3 months). Furthermore, the individual sport condition will also yield significantly larger changes in psychosocial outcomes than the personal time condition after 3 months of participation. Three additional secondary research questions will also be examined:
Can participation in the team sports and individual sports conditions be explained by the constructs of the Sport Commitment Model?We hypothesize that participation will be predicted by sports commitment as per the tenets of the Sport Commitment Model. Commitment will be predicted primarily by enjoyment (+), social constraints from family obligations/involvement alternatives (−), and social involvement opportunities/personal investments (+).Can group differences among these motivational and behavioral outcomes be explained through a mediation model?We propose that the covariance of the assigned conditions on psychosocial outcomes will be explained by sport participation. In turn, the covariance between participation and assigned conditions will be explained by salient underlying motives from the Sport Commitment Model. In particular, enjoyment will explain the differences between both sport conditions, but the better psychosocial outcomes from team sports will be explained by the additional involvement opportunities of friendship and social interaction.Is there a seasonal, gender, dual/single parent, age of child, or type of sport difference across primary outcomes by assigned condition?Differences in season, gender, age of child, and type of sport are exploratory research questions. It is possible that both sport conditions may have participation lowered by weather conditions in the winter. Men may participate in sport more due to lower childrearing expectations; however, there is currently limited research to support this conjecture. Similarly, younger children may impact sport participation because of the considerable care needs of young children. Finally, it is possible types of sport could differ in their psychosocial outcomes for reasons such as the structure or environment of participation.

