##### Quality of life

Psychosocial outcomes are primarily assessed using the 12-item Short Form Health Survey (SF-12) [33, 34], which measures health-related quality of life on a range of functional domains, including vitality, social functioning, and overall well-being. The domains assessed in the SF-12 have prior application in the sport domain [27, 35]. The SF-12 has been validated for adult populations, and there is established evidence for the reliability of scores derived from the instrument [34].

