#### Secondary outcome measures

##### Psychosocial outcomes and psychosocial distress

Additional quality of life outcomes are assessed via the Satisfaction With Life Scale, which has established reliable and valid test scores [36] and has been used in prior sport research [37]. Given our parent sample, we also measure relationship satisfaction with the Relationship Assessment Scale, which has shown adequate validity and reliability [38, 39], and parental stress with the previously validated Parental Stress Scale, which has shown a high level of internal consistency [40]. Finally, family functioning is assessed using the self-report Family Inventory Version II, which measures familial health/competence, conflict, cohesion, leadership, and emotional expressiveness [41].

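### The primary outcome is defined in two ways: five outcomes in the research question, but only the SF-12 (with no score chosen) in the outcome section, with three pairwise hypotheses attached

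*Protocol article*

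**What the plan says.** **Research question.** The section on aims and hypotheses asks "whether a team sport condition increases positive psychosocial outcomes (quality of life, relationship satisfaction, social functioning, perceived parental stress, enjoyment", at a primary endpoint of 3 months. The Abstract lists the same five: "quality of life, relationship satisfaction, social functioning, parental stress, and enjoyment".

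**Outcome section.** Under the primary heading there is one instrument: "Psychosocial outcomes are primarily assessed using the 12-item Short Form Health Survey (SF-12". It is described by its domains, "including vitality, social functioning, and overall well-being", and no domain or summary score is singled out. Under the secondary heading come two of the five outcomes: "we also measure relationship satisfaction with the Relationship Assessment Scale" and "parental stress with the previously validated Parental Stress Scale". Enjoyment is also there, as a construct of the sport commitment questionnaire.

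**Hypotheses.** Team sport is expected to exceed both other conditions, and individual sport is expected to exceed personal time. That makes three pairwise differences. Enjoyment is also a proposed mediator: "In particular, enjoyment will explain the differences between both sport conditions".

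**Analysis strategy.** A random-intercept model has a linear slope over three occasions. The team and individual sport indicators predict intercept and slope, with the control group as reference. The comparison of groups is then left to unspecified follow-up analyses.

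**The concern.** A trial should have one answer to the question of which result decides it. Here three of the five outcomes in the primary question are secondary in the outcome section. A fourth, social functioning, is one domain of the SF-12. The fifth, quality of life, has the SF-12 as its primary instrument and the Satisfaction With Life Scale as an additional secondary one.

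If the choice among outcomes, SF-12 scores and contrasts stays open until the data are seen, a positive headline can come from whichever one crosses the significance threshold. The reported p-value would then understate the risk of a chance finding.

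**Working it through.** **1. Where each outcome in the primary question is classed**

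| Outcome in the primary question | Place in the outcome section |
|---|---|
| Quality of life | Primary (SF-12, no score named); a further scale under secondary |
| Social functioning | A domain within the SF-12 |
| Relationship satisfaction | Secondary |
| Parental stress | Secondary |
| Enjoyment | Secondary (sport commitment questionnaire) |

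The two lists cannot both define the primary outcome.

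**2. Inputs for the error rate.** The document states no alpha and no family-wise error rate, so there is no figure of its own to reproduce. From the document: three equal arms (1:1:1), three contrasts, and one or five outcomes depending on the reading. Assumed: two-sided alpha 0.05 per test, no adjustment, no effect of any condition, and a common correlation r between outcomes of 0 to 0.9.

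**3. One SF-12 score, three contrasts.** The three contrasts share arms. At least one is significant when the range of three standardised arm means exceeds 1.96 × √2 = 2.77. The studentised range distribution for three means gives a probability of 0.122. Counting only results in the hypothesised direction, simulation gives 0.066.

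**4. Five outcomes, three contrasts (5 × 3 = 15 tests).** Simulation with 300,000 runs per setting:

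| r | Any of 15 | Any, hypothesised direction only |
|---|---|---|
| 0 | 47.9% | 28.8% |
| 0.3 | 44.6% | 25.5% |
| 0.5 | 39.4% | 22.4% |
| 0.7 | 32.7% | 18.3% |
| 0.9 | 23.2% | 12.9% |

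**5. Stricter reading of the lead hypothesis.** If team sport must beat both other arms on the same outcome, the chance of a false claim is about 0.5% for one outcome and 1.1–2.3% for any of five. If individual sport over control also counts as a success, it is about 3.0% for one outcome and 6–14% for five. These figures hold when no arm differs. If team sport truly beats one comparator but not the other, the false claim for one outcome can approach 2.5%.

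**6. Effect of a gate.** Suppose the contrasts are tested only after a significant two-degree-of-freedom test of condition. For one score the simulated family-wise error is 5.0%. For five outcomes, each with its own gate but no adjustment across outcomes, it is 10.4% (r = 0.9) to 22.6% (r = 0). Both steps are therefore needed: one outcome and a gate.

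**The case against.** The strongest reply is that the outcome section has an explicit primary and secondary split, says the SF-12 is the main measure, and should govern. The list in the research question would then be descriptive. On that reading, with one score, the inflation is at most about 12%. This limits the size of the problem but does not remove it: no score is chosen, and the research question and Abstract still say otherwise.

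A reader might infer that the trial has no error control. The documents do not support that. The article is silent on adjustment, it does not say the contrasts will be unadjusted or ungated, and a multiplicity rule is the kind of detail a statistical analysis plan may hold. The silence is not a finding in itself. A separate plan could not, however, make the research question agree with the outcome section.

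A reader might also infer that success may be claimed on any of 15 tests, with a false-positive chance of 1 − 0.95^15 = 54%. Nothing in the text says one outcome or one contrast suffices, and the lead hypothesis is directional and asks team sport to exceed both other arms. The 54% also treats the tests as independent. Because contrasts share arms, the figure is 47.9% even with uncorrelated outcomes.

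Lastly, enjoyment may be both an outcome and a mediator. The contradiction is only that it is in the primary question and under the secondary heading.

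**Conclusion.** The contradiction is real and internal to the article: five outcomes in the primary question, one instrument without a chosen score in the primary outcome section, and three pairwise hypotheses without a stated order or rule.

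Its size depends on the reading. With two-sided alpha 0.05 and no adjustment (both assumed), the chance of a false positive under no effect is about 12% for one SF-12 score and 23–48% if any of five outcomes counts. In the hypothesised direction only, the figures are about 7% and 13–29%. The five-outcome ranges span assumed correlations of 0.9 down to 0. Requiring team sport to beat both arms brings the chance well below these figures. A flat statement that the error is several times 5% would describe only the looser readings.

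**What to change.** 1. Name one SF-12 score, as change from baseline to 3 months, as the single primary outcome. Which score is for the investigators to decide on substantive grounds.
2. Bring the Abstract and the research question into line with the outcome section: relationship satisfaction, parental stress and enjoyment are secondary. Enjoyment may also remain a mediator.
3. In the planned model, first test the two condition-by-time terms jointly (two degrees of freedom, 5%), expressed as the difference between arms in change at 3 months. Only if that is significant, test the three pairwise contrasts at 5% each. With exactly three groups this is a closed procedure. If all arms are equal, the gate holds 5%. If only one pair is equal, only one true null is left, and it is tested at 5%.

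The gate leaves the pairwise alpha intact. Bonferroni at 0.05/3 would raise the simple two-sample requirement at effect size 0.40 and an assumed 80% power from 2 × (1.960 + 0.842)²/0.40², about 99 per arm, to 2 × (2.394 + 0.842)²/0.40², about 131 per arm.

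**Cost.** The other scales can no longer carry the primary claim. An ethics and registry amendment is needed. Because 109 parents had already completed 3 months when the article was written, the amendment should record that the choice was made without sight of comparative results.

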### Design

This study is a three-arm, parallel design, single-blind, randomized controlled trial. Written informed consent is obtained from participants before study enrollment. Participants are then assigned to one of three groups for a duration of 3 months: team sport choice condition, individual sport choice condition, or personal time control condition. Primary outcome measures in all three groups are assessed at baseline, 6 weeks, and 3 months. The design, conduct, and reporting of the trial has and continues to follow Standard Protocol Items: Recommendations for Interventional Trials (SPIRIT) guidelines [29] and will conform with Consolidated Standards of Reporting Trials (CONSORT) guidelines [30]. A SPIRIT checklist is provided as an Additional file and the SPIRIT diagram is included as Fig. 1. The randomized controlled trial is registered with the clinical trials registry maintained by the National Library of Medicine at the National Institutes of Health (ClinicalTrials.gov identifier NCT02898285).

**Fig. 1 Fig1:**
[figure not shown]
Schedule of enrollment, conditions, and assessments according to Standard Protocol Items: Recommendations for Interventional Trials (SPIRIT) diagram

### Participants and eligibility

Parents are considered eligible if they reside in Victoria, British Columbia, and have at least one child under 13 years of age who resides in the home. This cutoff was delimited as such because it represents the lower bound of the teenage years, when children still have substantial care needs. It follows parents with children under 13 have numerous familial obligations and subsequently experience notable time constraints. Both mothers and fathers are eligible, inclusive of those with single status. Parents must not engage in regular sport participation (operationally defined as not having participated in an organized sport in the month prior to baseline). Parents must also be below the recommended physical activity guidelines (150 min of weekly moderate to vigorous physical activity [19]), which is determined via self-report at the initial screening interview. Parents need to be willing to participate in a team sport in addition to being deemed safe to engage in moderate-intensity physical activity (assessed via the Get Active Questionnaire [31];). Those individuals who are not ready or able to participate in moderate-intensity physical activity will be excluded for safety reasons. Mental health conditions such as depression and anxiety do not preclude participation, because these are not contraindications to beginning a physical activity program [32].

